**8.4 Exploratory Analysis**

(1) Analysis of the effects of TOAST typing on specific therapy prescriptions in acute phase of AIS.

(2) Analysis of the relapse rate and the incidence of stroke dementia in three months after treatment.

**9 Patients complete / Withdraw from the study**

**9.1 Completion**

If the patient can provide all assessment data within the 90 days ± 14 days completely, this patient will be regarded as a completion case.

**9.2 Withdraw from the study**

If the patient experiences any of the followings, the patient should withdraw from this study:

- Wrong inclusion of the patient
- Withdrawal of informed consent
- When any other conditions occur, in the investigator's opinions, terminating this trial is to the subject’s best interests
- Lost to follow-up
- Other

The reason and date of withdrawal should be noted in the electronic Case Report Form (eCRF). Upon terminating the study, a last end-point evaluation should be done, except for lost of follow-up.

**10 Statistical methods**

The descriptive statistical method is adopted to perform the analysis on all the data. As for the measurement data, number of cases (missing number), mean value, median, standard deviation, first quartile, third quartile, maximum and minimum are described, and calculate the 95% confidence interval of the rates. Based on whether the score difference before and after treatment is in normal distribution, the paired t-test is adopted to make an inter-group comparison on measurement data, or the Wilcoxon signed rank test is used for analysis; χ ^2^ test or Fisher exact probability test is adopted to analyze the enumeration data; the Wilcoxon rank test is adopted to analyze the ranked data.

If needed, the missing data of visits in efficacy analysis will be filled in using last observation carried forward (LOCF) method.

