# Abstract of protocol

| Study title | Registration study on treatment outcome of Chinese acute ischemic cerebral stroke |
| --- | --- |
| **Sponsor** | Guangdong Techpool Pharmaceutical Stock Co., Ltd |
| **Principal Investigator** | [name], Peking University First Hospital |
| **Study staging** | Non-interventional case registration study |
| **Planned number of study sites and patients** | 10,000 cases |
| **Study schedule** | From March 2015 to March 2017, the expected inclusion time is 18 months |
| Study Background Overview | The stroke is one of the diseases seriously threatening people's health, and has the features of high incidence, high morbidity and high recurrence rate, among which the acute ischemic stroke accounts for about 70% to 80%. The patients will not only experience physical dysfunction, but disorders in mental state, social function and other aspects, which would seriously affect their quality of life, and bring a heavy burden on their families and the society. Therefore, the scientific and rational prevention and proper treatment of stroke is very important.  After the tireless research by scientists and clinical experts, a lot of achievements have been obtained for the prevention and treatment of AIS over the past decade. And in the whole world, there is still no adequately effective drugs or methods for the treatment of AIS, except for the ultra-early thrombolytic treatement and antiplatelet therapy with aspirin.  In China, the situation of the drugs for ALS is particularly complex, and, according to the relevant reports, there are more than 100 types of drugs for the clinical treatment of AIS. There was no data from clinical investigations of large sample size, to guide how to achieve good therapeutic effect, or possess a better cost - effectiveness through the combinations of different types of drugs. |

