| **Statistical methods** | A descriptive statistical analysis is made on the proportion of patients with good prognosis (mRS=0-2 points) and the proportion of patients with poor prognosis (mRS=3-5 points) and death (mRS=6 points) at 90 days after treatment, the corresponding number of cases and the proportion are calculated, and χ^2^ or Fisher's exact test is adopted to compare the inter-group difference. If the inter-group difference is of statistical significance, the Bonferroni method is adopted to adjust the size of test α value, and inter-group pairwise comparison is further made.  The changes in National Institutes of Health Stroke Scale (NIHSS) and EQ 5 visual analogue scale (EQ-5D) at discharge from baseline: if the score difference between before treatment and after treatment is in normal distribution and satisfied homoscedasticity, then analysis of variance is performed. If the statistical test results of the analysis of variance are of statistical significance, statistical analysis is further performed, and the Bonferroni test is carried out for pairwise comparison. Otherwise, the Kruskal Wallis method is adopted to perform statistical test. If the statistical test results of the Kruskal Wallis are of statistical significance, statistical analysis is further performed, and the Wilcoxon rank test is carried out, and the Bonferroni method is adopted to correct P value for pairwise comparison.  The descriptive statistical method is adopted to perform the analysis on all the data. As for the measurement data, number of cases (missing number), mean value, median, standard deviation, first quartile, third quartile, maximum and minimum are described, and the 95% confidence interval of the mean is calculated; as for the enumeration data, the frequency is described. It the hypothesis test needs to be carried out, the corresponding hypothesis test methods are adopted according to the nature of materials and the purpose of the test.  Unless otherwise specified, the hypothesis test adopted by this study is two-sided test with 0.05 as the size of test. P value ≤ 0.05 meant that the difference is of statistical significance.  Based on whether the score difference before and after treatment is in normal distribution, the paired t-test is adopted to make an inter-group comparison on measurement data, or the Wilcoxon signed rank test is used for analysis; χ ^2^ test or Fisher exact probability test is adopted to analyze the enumeration data; the Wilcoxon rank test is adopted to analyze the ranked data. |

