# 3 Overview of study design

This was a registered, prospective, multi-center clinical study. The study was planned to included 10, 000 patients with acute ischemic stroke (AIS) and record treatment regimens, treatment outcomes and medical expenses during hospitalization in real clinical practice. This study was to collect patients' data through a electronic data capture system (EDC).

According to the recommendations for treatment and follow-up observations in acute phase in the "Guidelines on diagnosis and treatment of acute ischemic stroke in China 2014 (Draft)", the patients with stroke were planed to receive 5 visits, which occurred at admission (baseline assessment, visit 1), 7 days ± 2 days after medication (visit 2), at discharge (visit 3), 90 days ± 14 days after medication (visit 4, outpatient service or telephone follow-up), and 360 days ± 28 days after medication (visits 5, telephone follow-up), respectively. As for the specifics, refer to [Study Flow Chart](#bookmark14).

In the baseline phase, the investigators should verify the inclusion/exclusion criteria, obtain the patients' informed consent, and try to collect the demographic information, past history, onset and admission conditions, and vital signs of the patients; and collect the following data of clinical examination: ECG, laboratory tests (blood routine, blood glucose, blood lipids, hepatic and renal functions, cardiac enzymes, serum electrolytes, coagulation) and imaging findings, and assess Glasgow Coma Scale, NIHSS score, mRS score and EQ-5D Scale. Seven days ± 2 days after medication, the vital signs of the patients were recorded and the NIHSS scores were accessed again. At discharge, the treatment regimen, vital signs, ECG and above laboratory tests results were recorded during hospitalization, and the Glasgow Coma Scale, NIHSS score, mRS score and EQ-5D scale were accessed, and the medical expenses during hospitalization was also collected. On 90 ± 14 days after medication, the recurrence of stroke, survival conditions and re-admissions were collected; the medical expense until this visits since discharge was recorded; and the mRS score, EQ-5D scale and MMSE scale (only applicable for the patients visiting the hospital) were accessed. On 360 days ± 28 days after medication, another telephone follow-up was given again, to ask the patient's health status, access mRS score, EQ-5D scale, and collect medical expenses.

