# 5 Treatment regimen

In the study, the doctors can select the specific treatment regimen for cerebral stroke according to the patient's clinical medical history and characteristics of symptoms as well as the China 2011 Guidelines for Diagnosis and Treatment of Ischemic Cerebral Stroke. This study has no limitations on the selection, dose and treatment course of the treatment drugs.

According toChinese Guideline for Diagnosis and Management of Acute Ischemic Stroke2010, The specific treatment on acute ischemic cerebral stroke refers to the intervention with a certain link in the pathophysiological mechanism of ischemic injuries. Examples are given to the following common drugs for illustration:

1. Intravenous thrombolysis drug: rt-PA and urokinase.
2. Anti-platelet drugs: aspirin and Clopidogrel
3. Anticoagulants: including unfractionated heparin, low molecular heparin, ateroid, oral decoagulants and thrombin inhibitor.
4. Volume expansion drug: hydroxyethyl starch, and low molecular dextran.
5. Nerve protective agents: Edaravone, nicholin and ganglioside.
6. Cerebral blood flow perfusion improving drugs: butylphthalide, human urine kininogenase (Urinary Kallidinogenase for Injection).
7. Chinese herbal medicines: Shuxuetong injection, and Danhong injection.

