**10.1 Determination of sample size**

For a more comprehensive collection of the patient information on the use of various drug combinations, this study protocol is planned to include 10,000 patients with acute stroke.

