**10.3 Analysis of efficacy**

FAS analysis is to be conducted for the efficacy indexes.

A descriptive statistical analysis is made on the proportion of patients with good prognosis (mRS=0-2 points) and the proportion of patients with poor prognosis (mRS=3-5 points) and death (mRS=6 points) at 90 days after treatment, the corresponding number of cases and the proportion are calculated, and χ^2^ or Fisher's exact test is adopted to compare the inter-group difference. If the inter-group difference is of statistical significance, the Bonferroni method is adopted to adjust the size of test α value, and inter-group pairwise comparison is further made.

The changes in National Institutes of Health Stroke Scale (NIHSS) and EQ 5 visual analogue scale (EQ-5D) at discharge from baseline: if the score difference between before treatment and after treatment is in normal distribution and satisfied homoscedasticity, then analysis of variance is performed. If the statistical test results of the analysis of variance are of statistical significance, statistical analysis is further performed, and the Bonferroni test is carried out for pairwise comparison. Otherwise, the Kruskal Wallis method is adopted to perform statistical test. If the statistical test results of the Kruskal Wallis are of statistical significance, statistical analysis is further performed, and the Wilcoxon rank test is carried out, and the Bonferroni method is adopted to correct P value for pairwise comparison.

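### The between-regimen tests treat patients from many hospitals as independent, so they reject too often wherever regimen choice follows hospital

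*Protocol*

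**What the plan says.** Section 3 describes the design: "This was a registered, prospective, multi-center clinical study". Section 10.1 gives the size: "this study protocol is planned to include 10,000 patients with acute stroke". The abstract has a row headed "Planned number of study sites and patients", but its entry is a patient count only, so the number of hospitals is not given. On treatment, section 5 says "This study has no limitations on the selection, dose and treatment course of the treatment drugs".

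The comparisons between regimen groups are named as follows:

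- **Section 10.3, 90-day mRS categories (including the primary endpoint):** chi-square, or "Fisher's exact test is adopted to compare the inter-group difference", followed by pairwise tests at a Bonferroni-adjusted level.
- **Section 10.3, changes in NIHSS and EQ-5D:** ANOVA if normality and equal variances hold. "Otherwise, the Kruskal Wallis method is adopted to perform statistical test", again with Bonferroni pairwise tests.
- **Section 10.4, symptomatic haemorrhagic transformation:** chi-square or Fisher.
- **Section 10.6, stroke recurrence and post-stroke dementia:** chi-square or Fisher, then Bonferroni pairwise tests.

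On intervals, section 10 says to "calculate the 95% confidence interval of the rates", while the corresponding sentence in the abstract says "the 95% confidence interval of the mean is calculated". Neither gives a formula. Nowhere is hospital a stratum, covariate, random effect or cluster. Section 10.7 refers to the SAP only for the content of interim analyses.

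**The concern.** The named between-group tests are valid when patients are independent. Patients treated in one hospital share case mix, staff, rehabilitation and outcome assessors, so their outcomes are likely to be correlated. When doctors may prescribe what they like, the regimen a patient receives may also depend on the hospital. If both hold, differences between hospitals show up as differences between regimens, and the standard error of the contrast is understated. Bonferroni does not repair this: it corrects for the number of comparisons, not for a variance that is too small.

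The stakes are practical. Section 1 wants the results to help clinicians choose drugs, and section 8.3 aims to identify the best in-hospital regimen. With 10,000 patients and an understated variance, spurious regimen differences can come with convincing p-values. The same mechanism affects the precision claimed for any overall prescribing or outcome rate, and the current treatment situation is the primary objective.

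**Working it through.** **Inputs from the protocol.** N = 10,000 (section 10.1). Two-sided 5% level (abstract, statistical methods). Illustrative prescribing rate 40%, the share that section 1 reports for a three-drug regimen in the sponsor's internal survey. The 10,000 comes with no power or precision calculation, so there is no figure of the plan's own to reproduce.

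**Assumptions.** Number of hospitals K = 50, 100 or 200, of equal size, so m = N/K = 200, 100 or 50 patients each. Outcome ICC 0.01 to 0.05. Regimen ICC from 0 (same mix in every hospital) to 1 (one regimen per hospital).

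**Regimen contrasts.** The approximate design effect for a two-group contrast is

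DEFF = 1 + (m − 1) × ICC(outcome) × ICC(regimen),

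and the actual error of a nominal 5% test is 2 × [1 − Φ(1.96/√DEFF)].

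This was checked by simulating the two-group pooled z test, which is equivalent to the uncorrected chi-square test. The simulation used N = 10,000, beta-binomial hospital effects, an assumed outcome rate of 65% and regimen share of 40%, no true regimen effect, and 1,500 runs. For K = 100 and outcome ICC 0.02:

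| Regimen ICC | DEFF | Error by formula | Error simulated |
|---|---|---|---|
| 0 | 1.00 | 5.0% | 4.9% |
| 0.1 | 1 + 99 × 0.02 × 0.1 = 1.20 | 7.3% | 6.3% |
| 0.3 | 1 + 99 × 0.02 × 0.3 = 1.59 | 12.1% | 13.7% |
| 1 | 1 + 99 × 0.02 × 1 = 2.98 | 25.6% | 28.1% |

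The Monte Carlo standard error is 0.6 to 1.2 percentage points, so formula and simulation agree reasonably well.

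In the extreme case of one regimen per hospital, the simulated error runs from 10.7% (200 hospitals, outcome ICC 0.01; DEFF 1.49) to 53.5% (50 hospitals, outcome ICC 0.05; DEFF 10.95).

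**A single rate.** Here DEFF = 1 + (m − 1) × ICC, with the ICC of the quantity being estimated.

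- Half-width as for independent patients, p = 0.40: 1.96 × √(0.40 × 0.60/10,000) = 0.96 points.
- K = 100, ICC 0.05: DEFF = 1 + 99 × 0.05 = 5.95.
- Clustered half-width: 0.96 × √5.95 = 0.96 × 2.44 = 2.34 points.
- Effective sample size: 10,000/5.95 = 1,681.
- Actual coverage of the uncorrected interval: 2Φ(1.96/2.44) − 1 = 58%.

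Over 50 to 200 hospitals and prescribing ICCs of 0.01 to 0.20, the correct half-width runs from 1.17 points (200 hospitals, ICC 0.01) to 6.13 points (50 hospitals, ICC 0.20).

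**The case against.** The strongest objection is that the protocol does not show that regimens follow hospital. Section 5 says doctors choose by the patient's history and symptoms, which implies variation within a hospital. If the regimen mix were the same everywhere, the chi-square test would keep its level (4.9% simulated). This stands. A reader might infer that every regimen contrast here has error bars that are too narrow, or that error rates of 40% or more are to be expected. The documents do not support either: inflation depends on how far regimen is tied to hospital, and the largest figures need every patient in a hospital to receive the same regimen.

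Second, the interval method is not specified. Independence is built into the named tests but can only be inferred for the intervals, and a variance formula may properly be left to the SAP. It is also unclear whether intervals on prescribing rates are planned at all: section 10 mentions rates within a sentence on measurement data, the abstract says mean at the same place, and prescribing by TOAST type is only listed. This stands too, so the remark on intervals is conditional.

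Third, the paired before-after tests in sections 10 and 10.4 are within-patient comparisons, and the regimen-by-hospital mechanism shown here does not apply to them. The point therefore does not extend to every test in the plan.

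The objection that the SAP may settle the between-regimen tests carries less weight. The protocol specifies them down to the pairwise procedure and defers only interim content, so a SAP that modelled hospital would depart from sections 10.3, 10.4 and 10.6.

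**Conclusion.** The point holds in conditional form. For between-regimen comparisons the protocol fixes tests that ignore hospital, in a design where regimen choice may well depend on hospital. With 100 hospitals and outcome ICC 0.02, the actual error of a nominal 5% test lies between about 5% and 28%, with 6% to 14% for regimen ICCs of 0.1 to 0.3. Intervals on overall rates would be too narrow under any positive ICC if computed as for independent patients, by a factor of about 2.4 at 100 hospitals and ICC 0.05.

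The direction is secure wherever outcome and regimen both cluster by hospital. The size is not, because hospital numbers and ICCs are assumptions and equal hospital sizes were used. This is an improvement worth making, not an error that invalidates the study.

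**What to change.** In section 10, state three things:

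1. Confidence intervals for rates use hospital as the cluster, with a robust variance.
2. Between-regimen comparisons in sections 10.3, 10.4 and 10.6 use a model with a hospital random effect, or GEE clustered by hospital, in place of the unadjusted tests. Bonferroni can stay for the pairwise contrasts.
3. A within-hospital comparison (stratified by hospital, or with hospital fixed effects) is a sensitivity analysis. It also removes confounding by differences between hospitals, which a random effect or GEE does not fully do.

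No new patients or visits are needed, and the patient's hospital is known in any multi-centre database. The costs are wider intervals, some added modelling, and a change to the stated primary-endpoint analysis, which is more than a change of wording. Hospitals that use only one regimen contribute nothing to the within-hospital comparison of regimens, and this should be reported.

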**10.1 Determination of sample size**

For a more comprehensive collection of the patient information on the use of various drug combinations, this study protocol is planned to include 10,000 patients with acute stroke.

**10.2 Analysis Data Sets**

All subjects who receive at least 1 dose of investigational drug and have at least 1 efficacy evaluation data after baseline are included in FAS, according to the basic principle of intention-to-treat (ITT) analysis.

**10.3 Analysis of efficacy**

FAS analysis is to be conducted for the efficacy indexes.

A descriptive statistical analysis is made on the proportion of patients with good prognosis (mRS=0-2 points) and the proportion of patients with poor prognosis (mRS=3-5 points) and death (mRS=6 points) at 90 days after treatment, the corresponding number of cases and the proportion are calculated, and χ^2^ or Fisher's exact test is adopted to compare the inter-group difference. If the inter-group difference is of statistical significance, the Bonferroni method is adopted to adjust the size of test α value, and inter-group pairwise comparison is further made.

The changes in National Institutes of Health Stroke Scale (NIHSS) and EQ 5 visual analogue scale (EQ-5D) at discharge from baseline: if the score difference between before treatment and after treatment is in normal distribution and satisfied homoscedasticity, then analysis of variance is performed. If the statistical test results of the analysis of variance are of statistical significance, statistical analysis is further performed, and the Bonferroni test is carried out for pairwise comparison. Otherwise, the Kruskal Wallis method is adopted to perform statistical test. If the statistical test results of the Kruskal Wallis are of statistical significance, statistical analysis is further performed, and the Wilcoxon rank test is carried out, and the Bonferroni method is adopted to correct P value for pairwise comparison.

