The acute ischemic cerebral stroke is the main cause that leads to the long-term disenabling, thus bring severe economic burdens[[10]](#bookmark11) to society and patient's family. Therefore, the performing of pharmacoeconomic evaluation on the different therapeutic regimens during the acute phase of cerebral stroke and the seeking of one or more kinds of drug therapeutic regimens with a high price/performance ratio which are suitable to the domestic conditions are of a higher social value. In the field of cerebral stroke treatment, currently there is rare prospective pharmacoeconomic evaluation domestically. Unlike the domestic cerebral stroke study fields which often adopt the cost effectiveness analysis (CEA)[[11]](#bookmark12), this study utilizes the cost utility analysis (CUA) for economic evaluation, the quality adjusted life years (QALYs) serves as the health outcome index, and the advantage of this method lies the measurement of life quality and the improvement of life-span (longevity) [[12]](#bookmark13). Considering the original intention of using this study as the registration study as well as the difficulty in expense collection, this study only collects the direct costs during the patient's hospitalization, and does not collect the indirect cost and implicit cost.

To sum up, this objective of this study is to analyze status quo of different drug combinations in the real world, evaluate the efficacy of different drug combination regimens in treating acute ischemic cerebral stroke, and perform cost-utility analysis. It aims to provide reference for a wide range of clinicians when selecting medications to treat acute ischemic cerebral stroke.

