**2 Study objective**

Primary study objective:

Analysis of current treatment situation in acute phase of acute ischemic stroke in real-world settings。

Secondary study objectives

(1) Comparison of effects of various drug combinations in treatment of acute ischemic stroke in real-world settings.

(2) Analysis of cost-utility of various drug combinations in treatment of acute ischemic stroke.

(3) Analysis of occurrences of complications and adverse events during treatment in hospital in patients with acute ischemic stroke.

(4) Analysis of effects of TOAST typing on specific therapy regimens in acute phase of acute ischemic stroke.

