**8.3 Pharmacoeconomic evaluation**

Calculate the cost/utility of the protocol of combinations of different drugs, and ascertain the optimal protocol of hospital treatment of patients with acute cerebral stroke. As for the costs, only the direct cost is collected, and the indirect cost and implicit cost are not collected. The direct costs in the study include:

- Direct medical cost (including the dug expense, examination expense, laboratory test expense, diagnosis and treatment expense, nursing expense and bed expense)

Discharge visit (Visit 3): Collect the direct medical cost according to the fees list of patients on discharge.

Visit 4 and visit 5: collect the direct medical costs by inquiring the patients or their families.

- Direct non-medical cost (including transportation expense, nutrition expense, family accompanying expense)

Directly collect the transportation costs and the nutrition costing by inquiring the patients or their families, and collect the nursing fees of the families by inquiring the families of the days/hours of downtime and calculating the fees through multiplying the days/hours by the local average wage.

In the utility analysis, quality-adjusted life years (QALYs) are used as the index of health outcome. The cost unit is Renminbi (RMB).

The QALY values are calculated through the utility value acquired by EQ-ED (evaluated on day 0 before treatment, at discharge,on 90 ± 14 days after treatment, 360 ± 28 days after treatment), and the pathway of the quality of life can be acquired by connecting the utility values on day 0, at discharge, on 90 ± 14 days after medication. With the time required for improving the quality of life as weights, we will get the QALY values. See the reference for the calculation method. [[14]](#bookmark16)

The EuroQol-5 Dimensions (EQ-5D) consists of two parts: the questionnaire and the conversion table of utility values. The questionnaires results can be used to describe the health status of the population and access to the EQ-VAS scores, and the EQ-5D index score can be further acquired by using the the time trade off (TTO) conversion table of utility values. Given that there is no suitable TTO conversion table of utility values in Chinese, the conversion table of utility values for Japanese is used to acquire the EQ-5D index scores. The following is the TTO conversion table of utility values in Japanese [[15]](#bookmark17):

| **Dimensions of EQ-5D** | **Level** | **Index** |
| --- | --- | --- |

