**10.4 Safety Analyses**

Descriptive statistics are mainly used for safety analysis. The incidences of symptomatic intracranial hemorrhage transformation between the groups are described statistically and compared by using the test of χ^2^ or the exact test of Fisher.

According to the relevant regulations of the state, the SAE incidence of the relevant product of the sponsor shall be described.

The vital signs and the laboratory test mesasurements shall be statistically described and compared by using Student's paired t-test and the Wilcoxon signed rank test befoer and after the baseline. The changes of laboratory test results and the ECC indexes are described with cross tabulations before and after the assessment.

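### The between-combination comparisons are fixed as tests unadjusted for case mix, although doctors choose the drugs from the patient's history and symptoms

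*Protocol*

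**What the plan says.** The abstract classes the study as a "Non-interventional case registration study". Under section 5, "the doctors can select the specific treatment regimen for cerebral stroke according to the patient's clinical medical history and characteristics of symptoms", and "This study has no limitations on the selection, dose and treatment course of the treatment drugs".

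Secondary objective (1) in section 2 is "Comparison of effects of various drug combinations in treatment of acute ischemic stroke in real-world settings". The introduction states the intended use: "It aims to provide reference for a wide range of clinicians when selecting medications to treat acute ischemic cerebral stroke".

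The between-group tests are fixed as follows:

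- **90-day mRS (section 10.3):** chi-square or "Fisher's exact test is adopted to compare the inter-group difference", then Bonferroni-adjusted pairs if the overall result is significant.
- **Change in NIHSS and EQ-VAS from baseline to discharge (section 10.3):** analysis of variance, or Kruskal-Wallis where its conditions fail, then Bonferroni pairs.
- **Symptomatic haemorrhagic transformation (section 10.4):** "The incidences of symptomatic intracranial hemorrhage transformation between the groups are described statistically and compared" by chi-square or Fisher; no pairwise step is named.
- **Recurrence and dementia (section 10.6):** chi-square or Fisher, then Bonferroni pairs.

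The statistical methods in the abstract repeat the section 10.3 tests. The protocol nowhere names regression, stratification, matching, a propensity score or covariate adjustment. It refers to the SAP only for the content of the interim analysis (section 10.7).

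**The concern.** When the doctor picks the regimen from the patient's history and presentation, patients on different combinations will tend to differ in prognosis before any drug acts. A crude test then compares patient mix and drug effect together and cannot separate them. A larger sample does not help: the bias stays the same while the standard error shrinks, so a false difference is declared more often.

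The only correction named, Bonferroni, limits chance findings across several pairs and leaves the bias in each pair untouched. The change scores do use the baseline NIHSS or VAS value. They do not make the groups comparable, because expected change itself depends on age, history, delay and severity. The 90-day mRS comparison, on the primary efficacy endpoint, uses no baseline data at all.

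At stake is a set of comparisons meant to inform the choice of drugs. This is not a detail left to the SAP, because the protocol positively specifies the unadjusted tests.

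**Working it through.** **What the protocol supplies.** Two-sided alpha of 0.05 (abstract, statistical methods) and 10,000 patients (section 10.1). The 10,000 comes without effect size, power, or number or size of groups, so it cannot be reproduced; this point does not depend on it.

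**What must be assumed.** Outcome rates by severity, the severity mix in each group, group sizes, and, for Bonferroni, four groups and hence six pairs. None of these is in the document. The drug effect is set to zero, so every rejection is false.

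**Step 1: crude rates, first set.** Good outcome 75% in mild and 30% in severe strokes; 30% severe in one group, 20% in the other.

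- Group A: 0.70 × 0.75 + 0.30 × 0.30 = 0.615
- Group B: 0.80 × 0.75 + 0.20 × 0.30 = 0.660
- Spurious difference: 0.045, or 4.5 points

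**Step 2: rejection rate of one pairwise test.** z = 0.045 / √[(0.615 × 0.385 + 0.660 × 0.340)/n], which gives 1.48, 2.10 and 2.96 at n = 500, 1,000 and 2,000 per group. The rejection rate is Φ(z − c), the opposite tail being negligible, with c = 1.960 at 0.05 and c = 2.638 at 0.05/6.

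| Patients per group | at 0.05 | at 0.05/6 |
|---|---|---|
| 500 | 32% | 12% |
| 1,000 | 55% | 29% |
| 2,000 | 84% | 63% |

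With a 5-point severity imbalance (25% against 20%), the spurious difference is 0.05 × 0.45 = 2.25 points. Rejection at 2,000 per group is 32% at 0.05 and about 13% at 0.05/6.

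**Step 3: a second set.** Good outcome 75% mild, 40% severe; 30% against 40% severe. Crude rates are 0.70 × 0.75 + 0.30 × 0.40 = 0.645 and 0.60 × 0.75 + 0.40 × 0.40 = 0.610, a difference of 3.5 points.

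| Patients per group | at 0.05 | at 0.05/6 |
|---|---|---|
| 1,000 | 37% | 15% |
| 2,500 | 73% | 47% |
| 5,000 | 95% | 84% |

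Four equal groups among 10,000 patients would be 2,500 each. The 5,000 row fits only two groups, so its 0.05/6 entry shows the trend and is not a case this study could reach.

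**Step 4: the overall test that comes first.** With four groups of 2,500, rates of 75%/40% and severe shares of 30%, 33%, 36% and 40%, the overall chi-square test rejects about 60% of the time with no drug effect. With shares of 28%, 30%, 32% and 34% it rejects about 25%.

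**Step 5: does adjustment remove it?** In 4,000 simulated studies per scenario, a Mantel-Haenszel test stratified by severity rejected 4.2% to 5.8% of the time wherever the mix was unequal. It does so because severity is the only confounder in the simulation; real data will have others.

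**The case against.** The best defence is that the primary objective is descriptive, the design is a registry, section 10.3 opens by calling the analysis descriptive, and safety is to be mainly descriptive. Nothing forbids an adjusted analysis later. This limits the reach of the point but does not answer it: a comparison of effects is a stated objective, and significance tests with pairwise follow-up go beyond description.

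The illustration can also be attacked. The outcome rates, severity mix and group sizes are all assumed, and the 0.05 column overstates a procedure that uses Bonferroni pairs after an overall test. That is why the 0.05/6 column is shown. The overall test can lower the pairwise rates further. They remain well above the nominal level in the first set and in the second.

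Four stronger readings are tempting, and the document does not support them:

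- **That the section 10.3 tests will name the best regimen.** The aim to "ascertain the optimal protocol of hospital treatment of patients with acute cerebral stroke" belongs to the cost-utility evaluation in section 8.3. Section 10.5 leaves its method of comparison open, and nothing feeds the section 10.3 tests into it.
- **That no analysis uses baseline data.** The NIHSS and EQ-VAS endpoints are changes from baseline.
- **That haemorrhage groups differ in severity by design.** The eligibility criteria contain onset-time conditions but no severity rule.
- **That objective (1) cannot be answered, or that the results will certainly be read as drug effects.** The data for an adjusted analysis are collected. The stated aim of guiding drug selection makes a causal reading plausible, not certain.

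**Conclusion.** The concern holds for the comparisons in sections 10.3, 10.4 and 10.6. Followed as written, the protocol tests non-randomised drug combinations without adjustment for case mix and offers only a multiplicity correction. With no drug effect and a 10-point severity imbalance, one pairwise test rejects 32% to 84% of the time at 0.05 and 12% to 63% at 0.05/6, for 500 to 2,000 patients per group with 75%/30% outcome rates. With 75%/40% rates the ranges are 37% to 95% and 15% to 84% for 1,000 to 5,000 per group.

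These sizes rest on the assumed rates, imbalance and number of pairs. That an imbalance in prognosis biases the crude contrast, and that rejection rises with sample size, does not. The plan should be changed before any between-combination result is reported; the descriptive primary objective is unaffected.

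**What to change.** In sections 10.3, 10.4 and 10.6, and in the matching abstract text:

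1. Keep the crude tables as description.
2. Define the combination groups in advance. Intravenous thrombolysis is itself one of the specific treatments listed in section 5. Where it is part of a combination, let it define or stratify the groups rather than enter as a covariate.
3. Base the comparison on adjusted models: logistic regression for mRS 0-2, and ANCOVA for NIHSS and EQ-VAS. Adjust for age, sex, baseline NIHSS, baseline mRS, onset-to-treatment time, prior stroke, atrial fibrillation and diabetes. Treat hospital as a random effect or use cluster-robust standard errors.
4. Where events are few, use a reduced covariate set or a propensity score.
5. Apply Bonferroni to the adjusted contrasts, and word the conclusions as associations.
6. Use the same adjustment in the cost-utility comparison, whose method section 10.5 leaves open.

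The patient-level covariates are already collected: Visit 1 records demographics, history, stroke onset time, NIHSS and mRS, and the discharge visit records when medication began. No new visits or patients are needed. The cost is rewording, more programming and usually wider intervals. Adjustment will not remove unmeasured confounding, and the report should say so.
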